## Abstract

**Background:**

University counselling services face a unique challenge to offer short-term therapeutic support to students presenting with complex mental health needs and in a setting which suits the academic timetable. The recent availability of mobile phone applications (apps) offers an opportunity to supplement face-to-face therapy and has the potential to reach a wider audience, maintain engagement between therapy sessions, and enhance therapeutic outcomes. The present study, entitled Counselling plus Apps for Students Experiencing Levels of Anxiety or Depression (CASELOAD), aims to explore the feasibility of supplementing counselling with guided use of a well-being app.

**Methods/Design:**

Forty help-seeking university students (aged 18 years and over) with symptoms of moderate anxiety or depression will be recruited from a University Counselling Service (UCS) in the United Kingdom (UK). Participants will be recruited via counsellors who provide the initial clinical assessment and who determine treatment allocation to one of two treatments on the basis of client-treatment fit. The two conditions comprise (1) counselling alone (treatment as usual/TAU) or (2) counselling supplemented with guided use of a well-being app (enhanced intervention). Trained counsellors will deliver up to six counselling sessions in each treatment arm across a 6-month period, and the session frequency will be decided by client-counsellor discussion. Assessments will occur at baseline, every counselling session, post-intervention (3 months after consent) and follow-up (6 months after consent). Assessments will include clinical measures of anxiety, depression, psychological functioning, specific mental health concerns (e.g. academic distress and substance misuse), resilience and therapeutic alliance. The usage, acceptability, feasibility and potential implications of combining counselling with guided use of the well-being app will be assessed through audio recordings of counselling sessions, telephone interviews with participants, focus groups with counsellors and counsellor notes.

**Discussion:**

This study will inform the design of a randomised pilot trial a﻿nd﻿ a definitive trial which aim to improve therapy engagement, reduce dropout and enhance clinical outcomes of student counselling.

**Trial registration:**

ISRCTN55102899

**Electronic supplementary material:**

The online version of this article (doi:10.1186/s40814-016-0119-2) contains supplementary material, which is available to authorized users.

## Background

There is limited evidence demonstrating the effectiveness of counselling services in higher education (HE), and recent government initiatives have negatively impacted on student services. These changes have been particularly noticeable in the United Kingdom (UK), since new policies have raised tuition fees and widened access to university without financially supporting service growth [1]. As a result, there is more pressure on university counselling services (UCSs) to demonstrate effectiveness and explore innovative solutions to continue to offer high-quality support with less resource in a sustainable way [2]. This is particularly challenging for student counselling services because they support a unique population with mental health needs that require counsellors/therapists who are trained and experienced in the academic context. For example, students require support that fits within the academic calendar and around periods of time when students are away from campus. Technology-assisted therapy provides a promising solution to support student counselling, but the feasibility and effectiveness of doing so are unknown [3, 4]. The current study aims to address these challenges by exploring the feasibility of supplementing face-to-face counselling with guided use of a well-being app for university students experiencing anxiety or depression.

### University counselling services (UCS) in the UK

UCSs are frequently evolving to address student demands and this has been widely accepted as a necessity [5, 6]. For example, a recent qualitative study summarised the changes experienced in a UK UCS [7]. These included the following prominent themes: (1) counsellors are being encouraged to work more flexibly by catering the number and frequency of therapy sessions to best suit their clients’ needs; (2) UCSs are offering more online support (e.g. online self-help) to manage growing demands with limited financial resources; (3) counsellors’ workloads are increasing to maintain high standards and meet growing demands in the absence of service expansion; (4) UCSs continue to be pressured to demonstrate effectiveness; and (5) there are concerns that UCSs may not be collecting the right type of data, not using the available data, or missing data after counselling. Furthermore, a recent investigation of the usage and acceptability of therapeutic technology in student counselling revealed that many services are interested in knowing how contemporary therapeutic technology, such as mobile apps, can be used in student services and the potential implications of doing so ([name], [name], & [name]: The burden of student mental health on embedded counselling services in UK Higher and Further Education institutions, submitted). Taken together, these findings demonstrate how UK UCSs are embracing change and exploring innovative solutions to address recent trends in student mental health.

### Feedback in therapy

In conjunction with finding new innovative solutions to address changes in UCSs, it is also important to explore whether existing methods can be enhanced to improve outcomes. One such method involves therapists providing feedback to clients about their responses on a clinical outcome measure in order to help clients acknowledge their progress or to raise discussion about adapting treatment. This method of integrating feedback into therapy has been widely explored and its impact on clinical outcomes have been summarised in a recent scoping review [8]. For example, compared to clients who received no feedback, clients who had feedback from clinical measures discussed in therapy (i) improved to a greater degree, (ii) demonstrated improvements sooner, (iii) required fewer therapy sessions, (iv) were less likely to drop-out of therapy and (v) maintained improvements at 6- and 12-month follow-ups. However, by contrast, a recent meta-analysis of 17 clinical trials found no significant differences between feedback and no-feedback groups on symptom outcomes [9]. Whilst there are mixed findings on the potential benefits of using feedback in therapy, the meta-analysis also concluded that the clinical trials exploring feedback in therapy exhibit strong bias and weak methodology.

Taken together, these mixed findings highlight the need for more rigorously designed clinical trials to explore the potential benefits of discussing feedback in therapy. Additionally, there is a need to understand the potential of augmenting therapy using technology, and monitoring feedback is a logical area in which to do this [10], given the ease with which mobile devices enable individuals to track various aspects of self-related data. Aside from the use of mobile technology to increase access to and uptake of psychological support, research demonstrates that therapeutic technologies can be cost-effective, acceptable, and show the potential to enhance the therapeutic process [11–13]. Therefore, whilst the positive findings regarding feedback relate to clinical outcome, the current study aims to apply the feedback model to discussing client thoughts, behaviours, emotions and activities monitored daily on a well-being app.

### The current study

The primary aim of the current study, offering face-to-face counselling, is to demonstrate whether discussion and guided use of a well-being app can be integrated into counselling sessions with university students experiencing anxiety or depression. This feasibility metric will be assessed through evaluation of therapeutic discussion from counselling audio recordings, telephone interviews with participants and a focus group with counsellors. Through this primary aim, the current study will also evaluate feasibility factors related to recruitment, acceptability, intervention delivery and clinical outcome monitoring. Therefore, the primary feasibility outcomes will comprise (i) recruitment duration to reach target sample size, (ii) client treatment preferences, (iii) acceptability of randomisation, (iv) intervention fidelity, (v) client/counsellor satisfaction and (vi) completion rate of follow-up measures. Secondary aims will explore the preliminary impact (in terms of effectiveness) and potential moderators for a fully powered definitive RCT. Preliminary impact will be assessed by comparing differences in therapeutic alliance between TAU and the enhanced intervention condition, as well as capturing participants’ views on the impact counselling has had on their well-being and ability to cope at university. Potential intervention moderators will include app usage during and between counselling sessions, as well as client characteristics.

## Methods/Design

### Study design

The feasibility trial utilises a two-arm, parallel non-randomised design comparing counselling alone (TAU) versus counselling supplemented with guided use of a well-being app and discussion of app activities (enhanced intervention) for university students experiencing anxiety or depression. This is displayed in Fig. 1. The feasibility trial was registered on the BioMed Central ISRCTN registry on 20/06/2016 under the acronym CASELOAD (Counselling plus Apps for Students Experiencing Levels Of Anxiety or Depression).

**Fig. 1 Fig1:**
[figure not shown]
Participant flow diagram for CASELOAD feasibility trial

### Ethical approval

This study received ethical approval from the University of Sheffield, Department of Psychology, Research Ethics Committee (REC) on 05/01/2016 (ref: 006171).^1^ The research-informed training programme within the current study also received separate ethical approval from the University of Sheffield, Department of Psychology, REC on 17/11/2015 (ref: 006727).

### Study setting

The trial will take place at the University of Sheffield UCS which receives approximately 1,300 student referrals annually.^2^ The UCS has an ethos of supporting research and embraced the proposed feasibility trial. Extensive joint meetings took place to discuss the trial design and, in particular, to ensure that its implementation is embedded into practice with minimal disruption to the service.

### Recruitment

In line with routine practice, students who approach the counselling service will be assessed by a counsellor to determine their appropriateness for counselling. Students who are approved for counselling (based on clinical judgement) will be provided with a study information booklet and invited to attend a 20-min research interview onsite to determine their eligibility. Leaflets, booklets and posters will also be displayed in the waiting room to raise awareness of the trial and encourage students to volunteer. Students who attend the research interview will be asked to provide written informed consent and will be assessed for eligibility through completion of the PHQ-9 and GAD-7. Eligible participants will be allocated to either the TAU condition or enhanced intervention according to the clinical judgement of the counsellor that provided the initial assessment.

### Allocation

This study is a non-randomised feasibility trial that aims to address the acceptability of randomisation prior to planning a pilot trial in preparation for a future definitive trial. Therefore, allocation will be based on counsellors’ clinical judgement of each student’s unique situation and primary reason for approaching the service. This will inform the acceptability and feasibility of randomising for the pilot trial. Participant allocation will also depend on whether the assessing counsellor is involved in the trial (based on availability) and whether the counsellor is participating in the provision of the enhanced intervention or TAU condition. Because the enhanced intervention relies on counsellors that are committed and trained to supplement counselling with a well-being app, participants assessed by counsellors in the TAU condition will not have the opportunity to join the enhanced intervention. However, participants assessed by counsellors in the enhanced intervention may be allocated to either condition as determined by their counsellor. Similarly, participants assessed by counsellors providing the enhanced intervention for whom the app is deemed inappropriate (e.g. client presents with inappropriate/excessive technology use or risk negative exposure to online communities for self-harm) will be allocated to TAU.

Considering these design elements, allocation will depend on the following factors: (i) whether the initial clinical assessment is with a counsellor who is part of the trial; (ii) whether the assessing counsellor is allocated to provide the enhanced intervention or TAU condition; (iii) the clinical judgement of the counsellor regarding whether participating in the trial would be appropriate for the client; and (iv) the clinical judgement of the counsellor regarding which intervention would be appropriate for the client. Whilst this allocation procedure is reliant on a counsellor’s clinical judgement, it is arguably the most appropriate allocation method for a non-randomised study and it keeps the client’s welfare in the forefront. Integrating a well-being app with face-to-face counselling with students experiencing moderate anxiety or depression is a new development with limited understanding of the implications. Therefore, using clinical judgement to inform the allocation will better monitor risk and feasibility metrics which counsellors will document to inform the screening criteria of a future randomised trial.

After the routine clinical assessment, participants will attend a one-to-one research interview (approximately 20 min) to provide written informed consent and determine eligibility before potentially joining the trial. During the research interview all participants will be informed about both treatment conditions and will be asked their preference (See later section on “Treatment preference”). The preference, as well as associated reasons for preference, will be recorded in the recruitment checklist information. Irrespective of the condition, participants will not be asked to cease using any existing well-being apps, but their use will be noted in the recruitment session and explored in the exit telephone interviews. Whilst the use of existing apps may pose risk of contamination, the enhanced intervention relies on the integration of app activity within counselling and participants in the control condition will not receive guided advice on the well-being apps they may use. In addition, group differences in outcome measures can be compared before/after participants are removed for using additional well-being apps. Combined, this information will be used to inform the recruitment rate, randomisation procedure, allocation procedure and blinding for a fully powered RCT.

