### Statistical analyses

#### Quantitative analysis

Analyses will be predominantly descriptive to characterise the study population and outline various feasibility metrics including recruitment rate, treatment preference, randomisation acceptability, treatment satisfaction and completion at follow-up. Whilst the sample size is not powered to detect significant differences between the TAU and enhanced intervention groups, data will be used to summarise outcomes from both groups to reveal preliminary trends and inform the design of the pilot trial from which estimates of effect and sample sizes will be calculated. Group comparisons will also be made between the demographic and baseline clinical measures to characterise the groups when they enter the trial. Determining potential baseline differences between the groups will inform whether the allocation procedure, which was dependent on clinical judgement, unintentionally created differences between the groups. Establishing these differences, or lack thereof, will further inform the potential group differences in clinical outcomes at the end of the feasibility trial. Outcome data will include the baseline prevalence and subsequent changes in depression (PHQ-9), anxiety (GAD-7), psychological functioning (CORE-10), student-specific mental health concerns (CCAPS) and emotional resilience (CD-RISC 10). Group summaries will also compare levels of therapeutic alliance (WAI) and treatment satisfaction (CSQ-8) in order to inform preliminary differences across treatments. No interim analysis will be performed; analysis will commence after completion of the 6-month follow-up. The distribution, variance and skewness of data will be initially explored to determine whether data should be described with parametric or non-parametric methods. Parametric descriptive statistics will include total score, mean, standard deviation, min, max and range. Non-parametric descriptive statistics will include total score, median, confidence intervals and inter-quartile ranges. Quantitative analyses will be performed with SPSS statistical software (version 22.0).

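### The check for differences created by allocation uses demographic and clinical measures, which capture only part of what counsellors allocate on, so similar scores cannot show that allocation created none

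*Protocol article*

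**What the plan says.** The Allocation section of the protocol article bases allocation on the counsellor's view of each student's "unique situation and primary reason for approaching the service". Clients of enhanced-condition counsellors for whom the app is judged inappropriate go to TAU; the examples given are that the "client presents with inappropriate/excessive technology use or risk negative exposure to online communities for self-harm". The assessing counsellor's own condition matters too: clients assessed by a TAU counsellor cannot enter the enhanced intervention. Under Counsellors, the minimum is 2 control and 4 intervention counsellors, who take a condition by preference.

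Under Quantitative analysis: "Group comparisons will also be made between the demographic and baseline clinical measures to characterise the groups when they enter the trial". The article says that finding such differences "will inform whether the allocation procedure, which was dependent on clinical judgement, unintentionally created differences between the groups". Its next sentence uses the result, whether differences are present or absent, to inform the reading of group differences in clinical outcomes. The Discussion adds that the comparison will help show whether outcome differences could be due to the app.

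**The concern.** The check is given a specific job: to say whether judgement-based allocation made the groups differ. It looks at variables that overlap only partly with those the judgement uses. If the demographic and clinical rows look alike, the plan as written lets that count as evidence of comparable groups, although the groups may differ in why clients attended, in whether the app was thought unsuitable for them, and in who assessed them. These could plausibly bear on satisfaction, alliance and symptom change. What is at stake is what the study can conclude about its own allocation procedure, and how far a difference in outcome summaries may be linked to the app.

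**Working it through.** **Figures in the plan.** There is none to reproduce. The article states: "Forty help-seeking university students (aged 18 years and over) with symptoms of moderate anxiety or depression will be recruited". It also says that "the sample size is not powered to detect significant differences between the TAU and enhanced intervention groups". No effect size or SD is given. The main check sets the sections side by side; the arithmetic after it is illustration.

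**1. Allocation factors against the comparison**

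| Factor (Allocation) | Covered by the baseline comparison? | Use stated for related data |
|---|---|---|
| Situation and main reason for attending | In part: CCAPS-62 at clinical assessment covers, among others, social anxiety, academic distress, eating concerns, substance abuse and suicide ideation | Assessment and session notes feed a client checklist and guide (Client characteristics) |
| App judged inappropriate | No: the listed CCAPS domains include neither technology use nor online exposure | Counsellor documentation informs screening for a later trial (Allocation) |
| Assessing counsellor's condition | No | Intra-therapist correlations on outcomes (Therapist effects), which is not a baseline comparison |

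No section compares the groups on the recorded reason for attending, the reason for allocation, app unsuitability or the assessing counsellor's condition.

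**2. How unequal the groups could be.** Assumptions: 40 clients; six counsellors with equal caseloads; a share d of all clients with a diverting feature; every such client of an enhanced counsellor diverted.

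- TAU route: 40 × 2/6 = 13.3. Enhanced route: 40 × 4/6 = 26.7.
- TAU n = 13.3 + 26.7d. Share with the feature in TAU = 40d / TAU n. Share in enhanced = 0.
- d = 0.10: TAU n = 16, share 4/16 = 25%.
- d = 0.25: TAU n = 20, share 10/20 = 50%.
- d = 0.40: TAU n = 24, share 16/24 = 67%.

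If the share seen by enhanced counsellors is varied from 50% to 80%, with d from 10% to 30%, the TAU share runs from 18% to 68%.

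Incomplete diversion shrinks the gap. With d = 0.25 and half of such clients diverted (also assumed), TAU has (3.33 + 3.33)/(13.33 + 3.33) = 40% and enhanced has 3.33/(26.67 − 3.33) = 14%. With no diversion both have 25%.

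The assessing counsellor's condition is unequal by rule. None of the enhanced group was assessed by a TAU counsellor. Under the full-diversion assumptions, 13.3/16 = 83%, 13.3/20 = 67% or 13.3/24 = 56% of TAU was.

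**3. What a clinical score would show.** If the feature correlates r with a score, the expected group difference in SD units is r / √(d(1−d)) × (TAU share − enhanced share). For r = 0.2 (assumed):

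- d = 0.10: 0.2/0.300 × 0.25 = 0.17
- d = 0.25: 0.2/0.433 × 0.50 = 0.23
- d = 0.40: 0.2/0.490 × 0.667 = 0.27

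For r from 0.1 to 0.3 the range is 0.08 to 0.41. SE = √(1/n_TAU + 1/n_enh): √(1/16 + 1/24) = 0.323 and √(1/20 + 1/20) = 0.316, so the 95% half-width is 1.96 × SE = 0.62 to 0.63 SD. Every one of these differences lies inside it.

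**4. Chance of noticing.** In 20,000 simulated trials of 40 clients (20% with the feature, two-thirds seen by enhanced counsellors, full diversion), a two-sided 5% test on one score flagged a difference in 4.7% of trials when the feature was unrelated to the score, 5.5% when carriers scored 0.2 SD higher and 10.0% when they scored 0.5 SD higher. With 20 per group, 80% power needs (1.96 + 0.84) × √(2/20) = 0.89 SD, and power at 0.5 SD is 35%. The article does not say that it will test baseline differences; the test stands in for any reading of the table.

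**The case against.** The strongest reply is that the check concerns differences created unintentionally. Diversion for app unsuitability is deliberate and declared, so it need not be rediscovered. That is fair for the first sentence about the check. It does not cover the next, which carries the result into the reading of outcomes, where deliberate sorting confounds as much as accidental sorting does.

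A second reply is that the rows of a baseline table belong in the full protocol or analysis plan, neither of which is shown, and that the article does not close its list. This stands against calling the rows missing. It does not remove the point, because the article names a set of measures and attaches to it a conclusion that the set cannot carry.

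Third, the study is descriptive and openly unpowered, and the pilot is to supply effect estimates. Recruitment, preference, randomisation acceptability, satisfaction and follow-up completion can all be reported without exchangeable groups. This stands and limits the consequence.

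Four stronger readings may tempt a reader, and the article does not support them:

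- **That stated preference and existing app use are sorting variables omitted from the check.** Neither is among the listed allocation factors, and both have a stated use. Preference informs bias from receiving the preferred condition (Treatment preference). For existing apps, "their use will be noted in the recruitment session", and outcomes can be compared with and without such users.
- **That presenting concerns are ignored.** CCAPS covers them in part, and Table 1 also places CORE-10, PHQ-9, GAD-7 and CD-RISC 10 before treatment.
- **That the rule guarantees unlike clients or near-complete imbalance.** Technology use and online exposure are examples only. Exclusion of high-risk students, and judgement that the trial is unsuitable for a client, may leave few to divert.
- **That the feasibility results are compromised.** They are not.

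**Conclusion.** The point holds in a limited form. Similarity on demographics and baseline clinical scores in about 40 clients cannot establish that allocation created no differences, because those measures reflect reason for attending only in part and do not reflect app unsuitability, reason for allocation or the assessing counsellor's condition. This follows from the text alone. Its size does not: 25% to 67% against 0% rests on assumed feature rates of 10% to 40%, equal caseloads and full diversion, and the gap falls to nothing if no one is diverted. The article gives no diversion rate. The consequence is confined to the conclusion about the allocation procedure and to the use of a null comparison when outcomes are read. It is worth correcting because the remedy is cheap.

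**What to change.** In Quantitative analysis, add to the comparison by condition:

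- the main reason for seeking counselling, taken from the intake data and assessment notes already listed under Client characteristics;
- the counsellor's recorded reason for allocation, including whether the app was judged unsuitable;
- the assessing counsellor's condition, so that TAU clients who came through an enhanced counsellor can be told apart from those who came through a TAU counsellor. This also yields the number diverted.

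Show existing app use and stated preference in the same table, labelled as potential confounders and not as variables that determined allocation.

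Add one sentence: similarity on demographic and clinical measures alone will not be read as absence of differences due to allocation.

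The cost is a few table rows and a short reason-for-allocation field at assessment. App use and preference are already collected, and no allocation decision changes. The downside is that the groups may look less comparable.
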